## Abstract

**Background:**

Maternal anemia is a leading public health issue placing pregnant women at higher risk of low birth weight, preterm birth, perinatal mortality, and neonatal mortality. Women in developing countries are at higher risk of anemia which could be either due to micronutrient deficiencies, hemoglobinopathies, infections or other socio-demographic factors. Thus, it is highly essential to explore the factors of anemia among women of the reproductive age group in order to design suitable interventions. The primary objective of this study is to assess the biological and socio-demographic factors that are associated with anemia among the women of the reproductive age group in Thatta district.

**Methods:**

An exploratory mixed method study using quantitative and qualitative approaches will be conducted in district Thatta Pakistan from September 2018 to January 2019. In the qualitative phase, data will be collected through focus group discussions and key informant interviews to understand the perceptions of women, their husbands and healthcare providers about anemia. In addition, a quantitative approach using cross-sectional study will be conducted to determine biological and socio-demographic factors associated with anemia. Approximately 150 non-pregnant women and their spouses will be included in the quantitative component of the study. In addition to thematic analysis for the qualitative component, Logistic regression will be done to calculate adjusted Odds ratios with their respective 95% CIs to assess the factors associated with anemia.

**Discussion:**

The better understanding of biological, socio-demographic factors and community perceptions of anemia will help us to design strategies and interventions to better address anemia during the reproductive cycle in rural areas of Pakistan. This will help the researchers and policymakers to take the appropriate action accordingly by designing suitable approaches to address the specific type of anemia in the rural population of Pakistan. This will, in turn, reduce the chances of adverse maternal and fetal outcomes associated with anemia.

## Plain English language summary

Anemia has been considered as a leading public health problem mainly among women of reproductive age group. This problem can be attributed to multiple factors such as consuming inappropriate diet, certain socio-demographic factors, susceptibility to develop some infections and hemoglobinopathies. Despite the similarities in the sociodemographic factors the prevalence of anemia widely differs between neighboring countries of India and Pakistan with high prevalence being found in rural Pakistan. Thus it is important to understand the factors associated with anemia in one of the rural districts of Pakistan. Given this condition, we propose to conduct a mixed method study using quantitative and qualitative approaches to study the biological and socio-demographic factors associated with anemia. In addition, this study will also provide an opportunity to explore the perceptions of women, their husbands and health care providers regarding anemia by conducting focus group discussions and key informant interviews. The better understanding of these factors and perceptions will help researchers and policy makers to design appropriate strategies and interventions in the rural areas of Pakistan to address the problem of anemia among women of reproductive age.

## Background

Maternal anemia is an important global health problem that affects about 500 million women of reproductive age [1]. As many as half of all pregnant women in low-income and middle-income countries are diagnosed with anemia [2, 3], which affects 32 million pregnant women worldwide [4]. Women in low-income and middle-income countries are at increased risk of anemia. This could be either due to the higher frequency of dietary micronutrient deficiencies such as iron and folic acid,, and infections such as malaria, HIV, and hookworm infestation in developing countries than developed countries [5]. Furthermore, the literature also highlights that prevalence of anemia may vary among pregnant women across low middle income countries due to differences in the lifestyles, socio-demographic and nutritional factors such as age, parity, educational and socioeconomic status, food insecurity, hygiene conditions, nutritional deficiencies and genetic predisposition that may determine the severity of anemia within the affected population [6, 7]. In addition, review of observational studies showed a linear association between maternal anemia and death, with each 10 g/l increase in maternal hemoglobin associated with a 29% reduction in maternal mortality (odds ratio [OR] 0·71 [95% CI 0·60–0·85]) [8].

WHO has recognized anemia as a global problem with serious consequence for mothers and their babies [9]. Even though anemia in pregnancy is readily treatable, data from several studies show an association between maternal anemia and severe adverse maternal and perinatal outcomes [3]. Moreover, there could be detrimental consequences of anemia during pregnancy, including the increased risks of low birth weight, preterm birth, perinatal mortality, and neonatal mortality [10].

In addition, maternal and newborn health registry (MNHR) has been maintained in 9 Union councils (UCs) of district Thatta, which documents birth outcomes and provide population-based rates of stillbirth, neonatal and maternal deaths [11, 12]. Recent MNHR data of 2017 also shows that 15.2% of pregnant women in these UCs are found to be severely anemic (Hb < 8 g. /dl), and 39.2% have been found as moderately anemic (Hb 8–10 g/dl) (Unpublished data). MNHR data also showed that severe anemia is more common in Pakistan as compared to India (0.2%) (unpublished data). Although both the India and Pakistan sites are quite similar in terms of their socio-demographic characteristics, there are huge differences in the proportion of women with very low Hb levels. Nevertheless, in both countries, the underlying cause of anemia needs to be explored across the range of socio-cultural and biological factors. Looking at these differences in the same area and with neighboring countries, it is highly essential to explore the factors of anemia among women of reproductive age group. In addition, through this study we will also explore the perceptions of women, their husbands and health care providers about anemia, its possible causes, how does it impact maternal and child health and what could be done to address this crucial problem in the district.

### Study purpose

The purpose of this study is to explore factors associated with anemia among women of the reproductive age group in Thatta district using mixed methods approach.

### Study objectives

#### The objectives of this study are two-fold

The objective for the qualitative phase includes:To explore the knowledge and perceptions of women, their husbands and health care providers about anemia, its possible causes, how does it impact maternal and child health and what could be done to address this crucial problem in the district.The objective for the quantitative phase include:To study the sociodemographic factors associated with anemia among women of the reproductive age group in Thatta District.To study the biological factors associated with anemia among women of the reproductive age group in Thatta District.To study the sociodemographic factors associated with anemia among men in Thatta District.

## Methods

This is an exploratory mixed method study using quantitative and qualitative approaches, including two study phases. In the first phase, a qualitative exploratory study will be conducted and the data will be analyzed to understand the perceptions of women, their husbands and healthcare providers regarding anemia. In the second phase, a quantitative approach using cross-sectional study will be conducted to determine factors associated with anemia. The general design of the study is presented in Fig. 1. The total duration of this substudy will be approximately 5 months (October 2018 to February 2019). The qualitative interviews will be conducted in Oct, 2018 and the data collection for quantitative phase will be from November to Dec 2018.The collected data will be analyzed and disseminated during Jan-Feb, 2018.

**Fig. 1 Fig1:**
[figure not shown]
Exploratory mixed method study

### Phase 1

#### Qualitative study

In this phase of the study, an exploratory qualitative research will be carried out using two semi-structured interview guides. The data collection methods for this phase will involve key-informant interviews (KIIs) and focus group discussions (FGDs). The aim of the FGDs and KIIs is to explore and understand the perceptions of women, their husbands and health care providers about anemia, its possible causes, how does it impact maternal and child health and what could be done to address this crucial problem in the district.

#### Study setting and participants

The study will be conducted at Thatta District Sindh Pakistan. Thatta is one of the rural districts of Pakistan located in the southernmost part of Sindh, bordering the two largest cities, Karachi and Hyderabad [13]. Despite its close proximity to these urban cities, Thatta was ranked 64th of 91 districts in the country on the Human Development Index in 2003 [14]. The newly formed district of Thatta now has four talukas (sub-districts) including Thatta, Mirpur Sakro, Keti Bander and Ghorabari. The Thatta district consists of 30 union councils (UCs), 257 Dehs, 3850 villages, 95,675 households (HHS) with the approximate population of 661,517, 81.6% of this population lives in rural areas of Thatta [15]. There are two public sector hospitals, 6 rural health centers (RHCs), 22 basic health units (BHUs) and 10 dispensaries in the district [16].

Despite the presence of multiple public and private schools, the total literacy rate of the district is 32.1%, where only 13% of women are literate [17]. Thatta has the lowest educational attainment score in the province and is ranked amongst the 5 lowest in the country [18]. On the other hand, Thatta does have a large number of health care providers, spread throughout the district and the proportion of women delivering at health care facilities is higher than the national average [19]. On average, 4.2 children are born to a woman during her childbearing years, while surprisingly only 10% of the women have reported using modern contraceptive methods of contraception (CPR) in the whole district [20].

The Global Network for Women’s and Children’s Health Research is the flagship research collaboration of the Reproductive Health research group in the Department of Community Health Sciences (CHS), Aga Khan University (AKU). This NICHD-funded Network is a partnership between US institutes and centers in developing countries in Asia (Pakistan and India), Africa (Kenya, the Democratic Republic of the Congo and Zambia) and Latin America (Guatemala). The Network aims to conduct multi-center trials of interventions for pregnant women, newborns, and children. In order to meet these objectives, CHS Department has maintained a Maternal Newborn Health Registry (MNHR) in Thatta District since 2008 in different geographic clusters where studies, both randomized controlled trials and cluster randomized trials of interventions to improve maternally and child health are carried out. A total population of around 170,000 is under continuous contact for research intervention.

Through MNHR, all pregnant women in the research clusters are identified registered and their outcomes are tracked for 6 weeks post-delivery. The detailed methods of the MNHR have been published elsewhere [11].

Likewise, other observational and interventional studies, MNHR provided a platform and existing research infrastructure to conduct an individually randomized controlled trial known as Woman First Trial (Preconception maternal nutrition). This trial aimed to determine the benefits to the offspring of women in poor, food-insecure environments of commencing a daily comprehensive maternal nutrition supplement ≥ 3 months prior to conception versus the benefits of commencing the same supplement at 12–14 weeks of gestation and also to compare offspring outcomes with those of a third trial arm who received no supplementation [21]. Study’s intervention included daily 20 g lipid-based (118 kcal) multi-micronutrient (MMN) supplement and, for women who were underweight or had slow gestational weight gain, an additional protein energy supplement was provided. The primary hypothesis of the study was that in women living in poor, food insecure populations, commencing a maternal nutrition supplement at least 3 months prior to pregnancy (Arm 1) would result in significantly greater fetal linear growth than starting the same nutrition supplement at 12–14 weeks gestation (Arm 2) or than not providing this supplement (Arm 3) [21]. The details of the Women First trial including design, study sites, follow-ups, various stages and ethical approvals are discussed in depth elsewhere [21].

For the current study regarding factors and perception of anemia, we propose to recruit conveniently mother-father pairs from 9 Union councils (UCs) of the district Thatta, where MNHR is currently based and subjects previously gave biological samples in Woman First (WF) trial. In addition, we will also enroll health care providers such as female and male doctors providing health services to the people of Thatta, traditional birth attendants (TBAs) who are one of the important stakeholders providing care to the women and lady health visitors or midwives who are also engaged in providing health care services to women Table 1.

**Table 1 Tab1:** Number of Participants for Qualitative phase

Number of participants for the qualitative phase	Sample Range
Participants for Key-informant Interviews (KIIs)	
Healthcare providers at District Thatta (Doctors/LHVs/TBAs/Managers)	10 KIIs
Participants for Focus Group Discussion (FGDs)	
The mother who were enrolled in WF trial	5 FGDs (6–8 participants in each group)
Male (husbands) of previously enrolled mothers in WF trial	5 FGDs (6–8 participants in each group)

#### Inclusion criteria

The study will include women and men who have previously participated in in WF trialThe study will involve key informants’ such as Doctors, TBAs, and LHVs who are willing to participate in the study.Participate who are willing to give consent will be included in the study

#### Exclusion criteria

Women who are pregnant at the time of data collection.Heath care providers, women and their husbands who do not agree to provide consent will be excluded.

#### Data collection method

Qualitative aspect will be covered by two components i.e. separate focus group discussions (FGDs) with women and their husbands and Key Informant Interviews (KIIs) with health care providers. Both of these will be conducted by developing separate guides which have been developed with the help of literature search and available expertise in the qualitative research. Prior to the actual research, the interview guide will be pretested to reveal any deficiencies in the study design.. This guide will include open-ended semi-structured questions along with probes to explore in-depth understanding about the anemia.

The questions will be exploratory in nature to encourage the free flow of information to elicit the important experiences and perceptions of the study participants regarding the women perception regarding balanced and adequate diet for a woman, anemia, risk factors and prevention and treatment of anemia. These interviews will be conducted by the principal investigator and research coordinator of the study. The interviews will be recorded after taking consent from the participants and the key points will be noted during the interview. Data collection will cease once the saturation will be achieved.

#### Data analysis

Data will be analyzed by using Nvivo 10 software. The study data gathered through FGDs and KIIs will be transcribed and translated from local language [Sindhi] to English and this would be analyzed via qualitative content analysis. The qualitative content analysis will be done to get the understanding of manifest content (what exactly transcript states) and the latent content (understanding the meaning of the transcript with context). The transcripts will be manually coded for data analysis. Transcripts will be proofread multiple times to get the correct understanding of the information provided by the participants regarding perceptions anemia. The main ideas on the transcripts will be selected and labeled as codes. Similar codes will then be analyzed and assembled into categories. In the final step subcategories with similar concepts will be grouped under the umbrella of themes. Two independent investigators to resolve the discrepancies and researchers bias will perform the coding, category formation, and thematic analysis.

### Phase 2

#### Quantitative study

In this phase of the study, a cross-sectional study will be conducted by using a structured and validated questionnaire to collect the data for this study. The questionnaire has been designed by taking validated questions form DHS (Demographic health survey) and Pakistan demographic health survey 2012–2013. The questionnaire will be consisting of socio-demographic and fertility-related information (age, marital status, parity, educational level, working status, socioeconomic status, religion, and place of residence) about the participants. This will also include all the related information for knowledge of contraceptives and its usage. Anthropometric measurements (weight, height, body mass index, waist circumference, hip circumference, mid-upper arm circumference, and head circumference.) will be conducted from enrolled women. Moreover, a 24-h dietary recall will be undertaken from enrolled women by using a 24-h dietary recall questionnaire which had also been used in the main WF trail for pregnant women in the same catchment area. This dietary recall questionnaire will help to assess the die consumed by women in district Thatta. In addition, socio-demographic characteristics of the enrolled husbands will be also collected on a separate one-page questionnaire.

The questionnaire will be pretested in the area having similar characteristics as that of the study site on the participants different from the study. The flow of questions and comprehensibility will be assessed during pre-testing the questionnaire. Refinement of the questionnaire will be done and refresher training of data collectors will be conducted by the Principal investigator and senior research coordinator of the study. This will be followed by actual and real administration of the questionnaire in the field.

#### Sample size and sampling method

A minimum sample of 150 women will be required in order to achieve a power of 80% at 5% level of significance, keeping proportion of anemia among women of reproductive age group from 21 to 75%, anticipated proportion of various risk factors in the range of 20 to 75% among anemic group and 20 to 82% among non-anemic group. In addition to 150 women, their spouses will also be included thus making a total of 300 participants to achieve the objective of quantitating phase of the proposed study. A probability simple random sampling technique will be used to select the participants. A sampling frame will be generated from existing data of WF participants and participants will be identified randomly from the given list by a third person mainly the data manager of MNHR.

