### Biological sample collection, transportation, and analysis

Two types of biological samples (blood and stool samples) will be collected from enrolled women in the proposed study. There are three different blood collection points in the catchment area of MNHR in district Thatta where samples will be collected. HVRAs will inform women at least 1 day before to collect biological samples from them and they will fix an appointment with them as per their availability and convenience. After informing women, HVRAs will visit women at their homes and will bring them to the blood collection points of AKU. Each sample collection is completely voluntary and can be denied at any time. Written informed consent will be obtained separately before any sample collection occurs.

At the blood collection point, a trained and qualified phlebotomist will greet the woman and explain the procedures of blood collection to her. The phlebotomist will collect blood samples from the woman by following universal precautions and standard procedures of AKU laboratory. A unique number and barcode will be assigned to each sample being collected from the woman and relevant information such as name and unique WF ID of woman and names of investigations (CBC, iron, B12 etc.) will be entered into the computer on the spot. The woman can submit the stool sample on the same day or she will be guided by HVRA to give stool sample the next day. A complete kit including clean sheet, gloves, Coleman box with ice packs and stool container with scoop will be provided to every woman to pass and store stool sample in a clean area on appropriate temperature. HVRA will contact the woman on the next day to inquire if she has passed stool sample and will collect the sample from woman to submit the same on appropriate collection point. This whole procedure of data collection along with biological sample collection will take about 60–90 min to complete the data collection from each individual participant.

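### The 80% power claimed for 150 women does not hold across the stated ranges, because no paired proportions or odds ratio are given

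*Protocol article*

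**What the plan says.** Under Phase 2, Sample size and sampling method, the protocol article says: "A minimum sample of 150 women will be required in order to achieve a power of 80% at 5% level of significance". Three inputs follow in the same sentence:

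- the proportion anemic: "keeping proportion of anemia among women of reproductive age group from 21 to 75" (percent);
- the risk factor proportions in the two groups: "anticipated proportion of various risk factors in the range of 20 to 75% among anemic group and 20 to 82% among non-anemic group".

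The section names no risk factor, pair of proportions, difference, odds ratio, sidedness or formula. The spouses bring the total to 300 but do not enter the comparison of anemic with non-anemic women.

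The Data analysis section for the quantitative phase says what the sample is for. Each biological and socio-demographic factor is compared between anemic and non-anemic women by an unadjusted OR with a 95% confidence interval. Factors with p below 0.25 then enter a multiple logistic regression.

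**The concern.** Power for a two-group comparison depends on the two proportions taken together. Separate ranges for each group do not fix it: these ranges overlap almost completely, so they allow anything from no difference to a difference of 62 percentage points. A single total cannot give 80% power over that span, yet the sentence attaches 80% to the whole set of factors.

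What is at stake is how the results are read. Many factors will be tested, and some will be non-significant. A reader who trusts the sentence could take each of those as a negative result from an adequately powered comparison, when 150 women can detect only large associations. The article says that its results should inform interventions and policy.

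**Working it through.** **Inputs.** From the sample size section: 150 women in total, 80% power, 5% level, 21 to 75% anemic, and the two exposure ranges. Assumption: a two-sided test, since sidedness is not stated.

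**Formula.** Two-proportion test with pooled variance under the null. Let π be the proportion anemic, n1 = 150π, n2 = 150(1 − π), p1 and p2 the exposure proportions in anemic and non-anemic women, and p̄ = πp1 + (1 − π)p2. Then

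- s0 = √[p̄(1 − p̄)(1/n1 + 1/n2)]
- s1 = √[p1(1 − p1)/n1 + p2(1 − p2)/n2]
- power = Φ[(|p1 − p2| − 1.96 s0)/s1]
- N = {1.96√[p̄(1 − p̄)(1/π + 1/(1 − π))] + 0.8416√[p1(1 − p1)/π + p2(1 − p2)/(1 − π)]}² / (p1 − p2)²

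Totals below round the anemic group up to a whole woman first.

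**Step 1: can 150 be reproduced from the ends of the ranges?** No.

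- 20% v 20%: there is no difference, so no N gives 80% power.
- 75% v 82%: N = 1,581, 1,080 and 1,471 at 21%, 50% and 75% anemic. At 50%: (1.96 × 0.8216 + 0.8416 × 0.8187)²/0.07² = (2.299/0.07)² ≈ 1,079, or 540 per group.
- 20% v 82%: N = 18 to 29.
- 75% v 20%: N = 24 to 34.

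**Step 2: power of 150 women at 75% v 82%.**

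- 21% anemic: (0.07 − 1.96 × 0.0794)/0.0848 = −1.01; power 15.7%.
- 50% anemic: (0.07 − 1.96 × 0.0671)/0.0668 = −0.92; power 17.9%.
- 75% anemic: (0.07 − 1.96 × 0.0797)/0.0749 = −1.15; power 12.5%.

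The highest value found was 18.2%, at 40% anemic. A one-sided test gives 21 to 28%. Even 150 women per group would give only 31%.

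**Step 3: which pairs do give about 150?** Interior ones. Examples are 20% v 41% at 50% anemic (N = 150) and 20% v 47% at 21% anemic (N = 148). The article states none of them.

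**Step 4: what 150 women deliver.** Setting power to 80% and solving for p1 gives, in each cell, the detectable proportion in anemic women and its OR. For example, 20% exposure at 50% anemic: (0.4089/0.5911)/(0.20/0.80) = 2.77.

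| Exposure in non-anemic women | 21% anemic | 50% anemic | 75% anemic |
|---|---|---|---|
| 20%, OR > 1 | 45.2%, 3.29 | 40.9%, 2.77 | 44.8%, 3.24 |
| 30%, OR > 1 | 57.1%, 3.10 | 52.3%, 2.56 | 55.9%, 2.96 |
| 50%, OR > 1 | 76.9%, 3.33 | 72.1%, 2.59 | 74.8%, 2.97 |
| 75%, OR > 1 | 95.5%, 7.06 | 91.9%, 3.77 | 93.1%, 4.47 |
| 20%, OR < 1 | 1.8%, 0.07 | 5.0%, 0.21 | 4.2%, 0.17 |
| 50%, OR < 1 | 23.1%, 0.30 | 27.9%, 0.39 | 25.2%, 0.34 |
| 75%, OR < 1 | 48.7%, 0.32 | 53.2%, 0.38 | 49.5%, 0.33 |

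At 40% exposure the ORs above 1 are slightly lower in the two right-hand columns: 3.12, 2.52 and 2.89. In the 75% row for OR > 1, the required proportion in anemic women (92 to 95%) lies above the protocol's own 75% ceiling for that group. The 0.07 is rough: it corresponds to about 0.6 exposed women among 31.5 anemic women, where the normal approximation is poor.

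**The case against.** The strongest defence is that the ranges summarize several factors. The low end in one group need not belong to the same factor as the low end in the other, so 20% v 20% and 75% v 82% are not pairs the protocol put forward. That stands. A reader might infer that the study was planned around a zero difference, or that 150 is a plain arithmetic error. The document supports neither: the ranges merely permit those contrasts, and interior pairs do give 150. The total may be correct for a particular factor, and the factor-by-factor calculation may sit in the full protocol, which is not shown.

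This does not rescue the sentence as printed. If 150 came from one factor, the 80% belongs to that factor and not to the whole set.

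Two further inferences go too far. First, sampling is optional ("Each sample collection is completely voluntary and can be denied at any time") and the section states no allowance for refusals, so one might conclude that the biological analyses will fall below 150 women. The article calls 150 a minimum and does not exclude inviting more, and it gives no expected loss, so any figure for the shortfall would be conjecture. Second, nothing says that the investigators will treat non-significant factors as unimportant. The plan reports ORs with 95% confidence intervals and calls the study exploratory. The risk lies in what the power sentence invites readers to assume.

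**Conclusion.** The concern holds in a limited form. The article attaches 80% power to 150 women for a whole set of risk factors but gives only marginal ranges, and over those ranges the claim is not true. With 150 women, power is 13 to 18% at one permitted contrast (75% v 82%), while other permitted contrasts need fewer than 35 women. The total of 150 follows only for pairs that are not stated.

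For factors present in 20, 30 or 50% of non-anemic women, 150 women give 80% power for unadjusted ORs above 1 of about 2.6 to 3.3. Commoner factors, and factors less common in anemic women, need stronger associations in most settings. These figures assume a two-sided 5% test, the pooled normal approximation, complete data on all 150 women and no adjustment. The planned adjusted analyses will generally have less power. The conclusion on the 80% claim does not depend on sidedness, continuity correction or the choice of variance formula.

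**What to change.** Replace the power claim with what 150 women deliver, for example:

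> With 150 women and a two-sided 5% test, there is 80% power for an unadjusted OR above 1 of about 2.6–2.8 if 50% of women are anemic, 3.0–3.2 if 75% are and 3.1–3.3 if 21% are, for factors present in 20%, 30% or 50% of non-anemic women. For factors present in 75% of non-anemic women, the detectable OR above 1 is about 3.8 (50% anemic), 4.5 (75%) and 7.1 (21%). For factors less common in anemic women, the detectable OR is about 0.2–0.4 at 50% anemic, and as low as 0.07 at 21% anemic when 20% of non-anemic women are exposed. Adjusted analyses have less power. A non-significant result will not be read as no association.

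If 150 was derived from one particular factor, name it, give its pair of proportions, the anemia prevalence and the sidedness used, and limit the 80% claim to that factor.

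The cost is one paragraph of text and a less favorable stated detectable effect. No participants, outcomes or analyses change.
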